## Abstract

**Introduction:** Amidst the evolving COVID-19 pandemic, understanding the transmission dynamics of the SARS-CoV-2 virus is key to providing peace of mind for the community and informing policy-making decisions. While available data suggest that school-aged children are not significant spreaders of SARS-CoV-2, the possibility of transmission in schools remains an ongoing concern, especially among an aging teaching workforce. Even in low-prevalence settings, communities must balance the potential risk of transmission with the need for students' ongoing education. Through the roll out of high-throughput school-based SARS-CoV-2 testing, enhanced follow-up for individuals exposed to COVID-19 and wellbeing surveys, this study investigates the dynamics of SARS-CoV-2 transmission and the current psychosocial wellbeing impacts of the pandemic in school communities.

**Methods:** The DETECT Schools Study is a prospective observational cohort surveillance study in 79 schools across Western Australia (WA), Australia. To investigate the incidence, transmission and impact of SARS-CoV-2 in schools, the study comprises three “modules”: Module 1) Spot-testing in schools to screen for asymptomatic SARS-CoV-2; Module 2) Enhanced surveillance of close contacts following the identification of any COVID-19 case to determine the secondary attack rate of SARS-CoV-2 in a school setting; and Module 3) Survey monitoring of school staff, students and their parents to assess psycho-social wellbeing following the first wave of the COVID-19 pandemic in WA.

**Clinical Trial Registration:** Trial registration number: ACTRN12620000922976

## Introduction

The first cases of COVID-19, a novel infection caused by the virus now designated SARS-CoV-2, were notified in December 2019 (1, 2). The subsequent global COVID-19 pandemic has elicited an unprecedented public health response, with many governments implementing disease control measures that most people have never previously experienced in their lifetime. Commonly implemented control measures include physical distancing, restrictions on public and private gatherings, closure of workplaces and hospitality venues, travel bans, and school closures (3). Three quarters of schools globally have experienced closures in 2020 (4). Across Australia, and indeed globally, whether schools are sufficiently safe and should remain open for staff and students remains a contentious and widely discussed topic. While it is important to stop the spread of COVID-19, predictions of increased economic, social, and psychological burden on families lead some to debate the wisdom of removing children from schools (5–7).

COVID-19 prevalence in Australia has been low relative to the global context, with just over 27,500 cases reported to October 30, 2020. The state of Western Australia (WA), with a population of ~2.5 million, has experienced only 775 cases, 9 deaths and no confirmed community transmission since April 2020. After a period of low school attendance and school holidays (March 15–April 29), during which parents were encouraged to provide home learning to their children, all students in WA were required to return to school from April 29, 2020. This call to return students to school sparked community concern about student and school staff safety. While existing data indicates the COVID-19 burden and rate of transmission in children and young people is much lower than adults (8–10), there is still much to be learnt about the transmission dynamics of SARS-CoV-2 in these younger age groups.

In addition to gaining an understanding of SARS-CoV-2 transmission in children and young people, the influence of social distancing measures such as school closures on their psychological health and wellbeing needs to be explored (11). Evidence suggests that children and adolescents have experienced increased levels of anxiety, irritability and inattention due to school closures (12), and that their online behaviors have been impacted, with young people engaging in more screen time for both educational and social purposes (13). Connectedness with friends and school can influence children and adolescents' life satisfaction, though to date it is unclear how these factors have mediated the influence of COVID-19.

In late April 2020, the WA government instigated the DETECT Schools Study in partnership with the Telethon Kids Institute to assess the prevalence and impact of COVID-19 in WA schools. The study, detailed here, seeks to quantify and characterize the transmission of SARS-CoV-2 in WA school settings while investigating the wellbeing of students, teachers, and parents during the pandemic.

## Study Design

The DETECT Schools Study is a prospective observational cohort surveillance study currently underway in 79 WA government schools, including education support settings and residential colleges. These schools are distributed across our large state, over an area of 2.6 million km^2^. Data collection will initially be conducted for 6 months and may be extended beyond this depending on the evolving COVID-19 situation.

### Aim and Objectives

The overall aim of the DETECT Schools Study is to better understand the burden, transmission, and psycho-social factors associated with COVID-19 in WA school communities. To this end, the study comprises three modules with distinct objectives:

Module 1 (asymptomatic SARS-CoV-2 testing): to investigate the prevalence of asymptomatic SARS-CoV-2 infection in a cohort of randomly selected school students and staff (in 40/79 participating schools).Module 2 (SARS-CoV-2 index case response): to determine the secondary attack rate of any SARS-CoV-2 infections detected in a WA school setting (in 40/79 participating schools).Module 3 (wellbeing factors associated with the COVID-19 pandemic): to elicit self-reported data on the physical, social and emotional wellbeing of students, their parents, and staff (in all 79 participating schools).

Modules 1 and 3 of the study are in progress, and Module 2 will be initiated as needed.

### Stakeholders/Partnerships

The DETECT Schools Study is a WA Government initiative, coordinated by the Telethon Kids Institute in partnership and consultation with the WA Departments of Health and Education. Study design, operational oversight and data interpretation is led by the Telethon Kids Institute study team. School selection and management is coordinated by the Department of Education. Swab testing is coordinated by the Department of Health: samples are collected by the Child and Adolescent Health Service (CAHS) and the WA Country Health Service (WACHS), and SARS-CoV-2 testing is performed by public laboratory service provider PathWest.

### Patient and Public Involvement

Community involvement and advice was actively sought in the design and preparation of this study and will inform the analysis and dissemination of findings. A National Community Advisory Group for COVID-19 Research, convened by the Telethon Kids Institute, reviewed and provided feedback on procedures and resources including consent forms and surveys to aid in the development of content most appropriate for potential study participants, including children with disabilities. This panel comprised community members from across Australia, including Aboriginal members. Telethon Kids Institute Kulunga Aboriginal Research Development Unit provided advice regarding communications with Aboriginal families who may be involved in the study, including culturally-secure and informed consent processes and measures for supporting Aboriginal families during Module 2, which requires swabbing and symptom checking to take place within the home. Further, advice was sought from the Department of Education and the four participating education support schools to develop visual communication tools to increase accessibility of the survey for students in these settings.

While considerable time was spent refining the DETECT Schools Study protocol and resources, the study proceeds with an acute awareness that implementation may well bring to light additional considerations or challenges. As such, consultation with these advisement bodies is ongoing and will continue to be critical in informing the trial as it progresses.

### Study Methods

#### School Selection and Group Assignment

Eighty schools were selected for participation by the Department of Education, ensuring the inclusion of broad representation across state geography, primary and secondary schools, and specialist facilities including residential colleges and education support settings. A variety of practical considerations with respect to maximizing school participation and project feasibility were considered. Consequently, school selection did not follow a strict randomization procedure from all schools state-wide, although care was taken to minimize biased selection based on any *a priori* criteria. The potential for bias due to this non-random selection will be addressed during data analyses, where sample weightings will be employed to adjust for under- or over-representation across the geographical and demographic characteristics of each school, as determined from Australian Bureau of Statistics (ABS) census data.

The eighty participating schools were stratified into 10 groups by geographical region and school classification (Table 1).

**Table 1 T1:** Stratification of DETECT Schools by geographical region and school type.

	**North metro**	**South metro**	**Regional**
Primary	12	12	12
Secondary	12	12	12
Educational support setting	2	2	–
Residential college	1	3	

Within each stratum, schools were allocated to either the swab testing or non-swab testing groups by a simple randomization procedure. Forty schools were randomly allocated to the swab testing group and were invited to participate in Modules 1 (asymptomatic SARS-CoV-2 testing), 2 (SARS-CoV-2 index case response) and 3 (wellbeing survey). The remaining 40 schools were randomly assigned to the non-swab testing group and were invited to participate in Module 3 only. Following recruitment and randomization one non-swab testing metropolitan secondary school opted out of the study, leaving 79 participating schools.

#### Consent Process

Distinct consent was sought for each study module. Invited participants consented to the three study modules (swab testing group) or Module 3 only (non-swab testing group) at the beginning of the study through one online consent process supported by the REDCap platform (14). Participation in each module is stand-alone, and individuals can choose not to participate in any module without affecting their participation in other modules.

Modules 1 and 2 require active consent from participants, collected from staff and students' parents/guardians at the 40 swab testing schools. Consenting individuals (or guardians) complete a consent form in the study database and may subsequently withdraw at any time.

For Module 3, a passive consent approach is adopted for students: parents are required to actively “opt-out” their child from participating and the survey is offered to all students who have not opted out. Previously, application of an opt-out consent framework nationally by the Australian Early Development Census (AEDC) resulted in a minimum participation rate of 95%, serving to minimize selection bias and maximize the reliability and generalisability of the research data collected. The use of student passive consent for this module was supported by the consumer reference group and ethics committees. Parents and staff provide active consent to participate but may opt out of participation at any time.

#### Module 1 Methodology

Module 1 entails combination throat and nose SARS-CoV-2 swabbing of asymptomatic students and staff to quantify how much (if any) asymptomatic infection is present in schools. Students at school on the day of testing are assumed to be asymptomatic, as the Department of Education has adopted a policy supporting families to keep any children with COVID-19 symptoms at home. From the consented population, up to 150 randomly selected students and staff are swabbed in each school per round, with staff comprising 10% of the sample.

##### Exclusion Criteria

Participants are excluded from swabbing if they have experienced any of the following:

More than one nosebleed per week.Recurrent vomiting, particularly if triggered by a gag reflex.Large/problematic tonsils awaiting tonsillectomy.Significant anxiety about medical procedures.

During the consent process, parents were asked to confirm that their child(ren) did not meet the exclusion criteria. Staff were asked to self-assess against the exclusion criteria.

##### Randomization for Swab Testing

Three to six rounds of swabbing will be conducted, approximately monthly. Of students and staff who provided active consent, 150 will be randomly selected from each school in each round. Student grade level groups will be stratified into two strata per school (younger and older halves of students, depending on the total age demographic of the school). Randomization will be conducted within the REDCap database using a simple random number algorithm, generating a list of 200 consenting participants: 45% students from each stratum and 10% staff. If a randomized student or staff member is not available or does not assent to testing on the day, they will be replaced by the next available consenting participant from their stratum until 150 swabs are collected.

##### SARS-CoV-2 Swabbing

SARS-CoV-2 swabbing will be carried out by a team of nursing staff. The participant's information will be verified to ensure consent has been obtained, and if for any reason identification and therefore consent cannot be confirmed (e.g., student indicates a date of birth different to that captured during the consent process), then swabbing will not continue with that individual. All participants will be asked to verbally assent prior to swabbing being performed. An oropharyngeal (OP) swab (tonsillar beds and the back of the throat, avoiding the tongue) and subsequent nasal (Na) swab (along the floor of the nasal cavity parallel to the palate to a depth of 1-2 cm before resistance is encountered at the nasal turbinates) (Figure 1) will be taken sequentially with a single fine flexible shaft flocked swab (CITOSWAB Flocked Swab, Gaia Science, Singapore) and placed into virus transport media (VTM). If at any point the participant indicates they would like to stop or displays signs of distress, swabbing will not proceed.

**Figure 1 F1:**
[figure not shown]
Combined oropharyngeal and nasal (OP/Na) swabbing with a single fine flexible shaft flocked swab.

The combined oropharyngeal and anterior nasal (OP/Na) swab employed for this study is not the same as the nasopharyngeal swab commonly used for clinical SARS-CoV-2 diagnosis. OP/Na swabbing is significantly less invasive and therefore less likely to cause discomfort. This allows for the swabbing of students without a parent present, minimizes discomfort and optimizes the rate of assent amongst participants. Recent research indicates that OP/Na swabbing has comparable specificity and sensitivity to nasopharyngeal swabbing for SARS-CoV-2 detection (15). This swabbing approach aligns with the current recommendations from the Communicable Diseases Network Australia (CDNA) COVID-19 National Guidelines for Public Health Units (version 3.6, 30 July 2020), which states that for most patients with mild illness (this is the closest to asymptomatic), collection of OP/Na swabs is a low risk procedue that can be performed with appropriate contact and droplet precautions. Testing staff will wear an apron, mask and eye shield at all times when testing, and a new pair of disposable gloves for each participant.

##### Laboratory Analysis of Swabs

Polymerase chain reaction (PCR) testing of all swabs for SARS-CoV-2 will be carried out at PathWest using an in-house PCR platform of high analytical sensitivity and specificity with appropriate positive and negative controls. To reduce the chance of a false positive result, any sample which returns a positive result will undergo confirmatory testing with the GeneXpert SARS-CoV-2 PCR platform (Cepheid, California, USA). Testing of asymptomatic participants has the greatest risk of returning an unexpected false positive, and use of a second platform with robust internal controls will minimize the risk of reporting a false positive result.

##### Notification of Swab Results

Under the Public Health Act 2016 of WA, COVID-19 is a notifiable disease. Any negative SARS-CoV-2 results will be communicated to participants directly by text message from PathWest, in line with standard clinical care notification procedures. In the instance of a positive SARS-CoV-2 result, PathWest will notify the WA Health Communicable Diseases unit, who will initiate standard contact tracing procedures with the confirmed case and liaise with the key contact for the relevant school to ensure appropriate public health action. The Department of Education recommends closure and deep cleaning of any school in which an index case presents, and this will be actioned by the Department of Health. At all times, the identity of the positive case will be kept confidential.

For study data analysis, all SARS-CoV-2 results will be communicated to the study team by means of a secure and confidential file transfer.

##### Swab Testing Sample Size Calculation

The study sample size (40 schools, 150 sampled individuals at each school per month, for 3–6 months) is calculated with intent to achieve as broad and representative a sampling frame as possible. Taking into account practical considerations such as constraints on school participation and feasible total number of samples per month, and given the potential sources of bias and imprecision inherent with these constraints and the likely very low prevalence rate, the task of estimating state-wide infection prevalence among school populations does not lend itself to simple statistical analysis. As such, this study will employ a sophisticated approach validated using simulated data, which explores its performance in a range of different community transmission intensity scenarios.

##### Data Analysis

This study seeks to design a robust yet efficient estimator for the prevalence of SARS-CoV-2 infections amongst the general population of school children and staff in WA based on Module 1 testing data. The challenge will be to bound the range of plausible sampling distributions that might arise from observation through the given survey design of the epidemic spread of this virus, especially given the many uncertainties that remain concerning SARS-CoV-2 transmission dynamics.

Under these uncertain epidemic conditions, standard approaches to prevalence estimation based on adjustment by estimated design effects for representing intra-cluster correlation may perform unfavorably. A solution for this unique situation is to adopt an estimator designed specifically for robustness against model misspecification. Analysis of Module 1 data will employ a weighted likelihood bootstrap with Bayesian regularization. This nominal model supposes a Poisson sampling distribution with a Gamma distribution prior on the unknown rate equivalent to a single prior observation of one positive case amongst 6000 (40x150) individuals.

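### The Module 1 model targets infection prevalence but has no detection term, so as written it estimates confirmed PCR positivity

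*Protocol article*

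**What the plan says.** The Module 1 Data Analysis section seeks a "robust yet efficient estimator for the prevalence of SARS-CoV-2 infections amongst the general population of school children and staff in WA". The method is then fixed: "Analysis of Module 1 data will employ a weighted likelihood bootstrap with Bayesian regularization". The core model follows: "This nominal model supposes a Poisson sampling distribution with a Gamma distribution prior on the unknown rate", the prior being "equivalent to a single prior observation of one positive case amongst 6000 (40x150) individuals".

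Three other places bear on how a positive comes about.

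- **Swab.** The text with Figure 1, in SARS-CoV-2 Swabbing, says that "OP/Na swabbing has comparable specificity and sensitivity to nasopharyngeal swabbing for SARS-CoV-2 detection". This is a comparison with another swab, and no figure is given.
- **Laboratory.** Laboratory Analysis of Swabs describes the in-house PCR as having high analytical sensitivity, again without a figure. It adds that "any sample which returns a positive result will undergo confirmatory testing with the GeneXpert SARS-CoV-2 PCR platform", for the stated purpose of limiting false positives. False negatives are not discussed.
- **Validation.** Swab Testing Sample Size Calculation gives the design as "40 schools, 150 sampled individuals at each school per month, for 3–6 months" and says that "this study will employ a sophisticated approach validated using simulated data, which explores its performance in a range of different community transmission intensity scenarios". Test error is not among the features named.

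**The concern.** The target is infection, and the data are confirmed positives. The stated rate and its prior are both expressed in positive cases, with nothing between them and infection.

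Two features of the testing make the gap matter. A swab comparable to a nasopharyngeal swab is comparable to a test that can itself miss infections, and analytical sensitivity describes the assay rather than the detection of infected people. Retesting only the positives protects specificity, but it cannot raise sensitivity and may lower it.

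The safeguards the article names address other problems: school weighting for non-random selection, and the bootstrap for clustering and uncertain transmission. Reweighting observed results cannot recover infections recorded as negative, so the estimate stays centred on the detected rate.

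The Discussion says the results will advise the community and feed state policy on whether asymptomatic infection in schools is rare. Compared with a corrected analysis, the omission moves the estimate and its upper limit towards reassurance.

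**Working it through.** **Inputs from the article.** 40 schools, 150 people per school per round, 3 to 6 rounds; prior worth one positive case in 6,000.

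**Assumptions.** Net sensitivity *Se* is not stated, so I use 0.6 to 0.95. Specificity is taken as 1. The prior is read as Gamma(shape 1, rate 6,000). Prevalence is held constant over rounds. School weights, clustering and the bootstrap are not reproduced, because the article does not give enough detail; what follows is the conjugate core of the stated model.

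**Step 1: the article's own figure.** 40 × 150 = 6,000, as stated. Three rounds give 18,000 swabs and six give 36,000. The prior mean is 1/6,000 = 1.67e-4. The article gives no precision or upper limit to reproduce.

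**Step 2: model as stated.** With *x* positives in *n* swabs the posterior is Gamma(1 + x, 6,000 + n). With x = 0 its 95% quantile is −ln(0.05)/(6,000 + n).

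**Step 3: with a detection term.** If x ~ Poisson(n × Se × p) and the prior stays on true prevalence *p*, the posterior for fixed *Se* is Gamma(1 + x, 6,000 + n·Se). The mean and every quantile rise by (6,000 + n)/(6,000 + n·Se):

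| Se | 1 round | 3 rounds | 6 rounds |
|---|---|---|---|
| 0.95 | 1.03 | 1.04 | 1.04 |
| 0.80 | 1.11 | 1.18 | 1.21 |
| 0.60 | 1.25 | 1.43 | 1.52 |

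If the prior is placed on the detected rate instead, the factor is 1/Se: 1.05, 1.25 and 1.67.

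**Step 4: uncertain sensitivity, zero positives.** With *Se* uniform on 0.6 to 0.9, the limit *u* solves ∫ w(s) exp(−(6,000 + n·s)u) ds = 0.05, where w(s) is proportional to 1/(6,000 + n·s).

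| Rounds | 95% limit as stated | 95% limit with Se | Factor |
|---|---|---|---|
| 1 | 2.50e-4 | 2.87e-4 | 1.15 |
| 3 | 1.25e-4 | 1.56e-4 | 1.25 |
| 6 | 7.13e-5 | 9.29e-5 | 1.30 |

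**Step 5: against the truth rather than against a corrected analysis.** Under the stated model the expected posterior mean is (1 + n·Se·p)/(6,000 + n). It equals *p* at p = 1/(6,000 + n(1 − Se)). For Se = 0.80 this is 1/7,200 = 1.39e-4 with one round and 1/13,200 = 7.6e-5 with six. Below that point the uncorrected estimate is on average above the truth, and above it the estimate is below. Coverage of the upper 97.5% limit with six rounds:

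| True prevalence | Se 1 | Se 0.8 | Se 0.6 |
|---|---|---|---|
| 4e-5 | 100% | 100% | 100% |
| 1e-4 | 97% | 94% | 88% |
| 2e-4 | 97.5% | 93% | 81% |
| 5e-4 | 91% | 68% | 29% |

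At 2e-4, for example, the limit covers when x ≥ 3, and x is Poisson with mean 36,000 × Se × 2e-4, which is 7.2, 5.76 and 4.32 across the row.

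**Step 6: specificity.** With assumed specificities of 0.999 and 0.99 for the two platforms, false positives per round are 6,000 × 0.001 × 0.01 = 0.06. They do not offset the missed infections to any useful degree.

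**The case against.** The strongest objection is that the error is inferred from silence. This is a condensed article, the model is called nominal, the estimator is chosen for robustness to misspecification, and the simulation work and any analysis plan are not shown. A reader might infer that the trial assumes a perfect test. The article does not say so, nor does it say that results will go uncorrected. That part of the objection stands. What remains is that the article fixes the likelihood, the prior and the prior's weight, calls the target infection, and leaves no place for detection. Robustness of the kind described does not supply one.

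A reader might also infer that the estimate and limit are always too low. The figures do not support this. At a true prevalence of 4e-5, which matches the 0.004% UK student figure in the Discussion, the prior puts the expected estimate at 2.38 to 2.48 times the truth with one round and 1.11 to 1.28 times with six, for sensitivity 0.6 to 0.8. The limit covers in every case. At higher prevalence, part of the shortfall comes from the prior: at 5e-4 with six rounds, coverage is already 91% at sensitivity 1.

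Two further points stand in part. Every size rests on an assumed sensitivity, and treating retest failures as negative is implied rather than stated. The comparators in the Discussion run from 0.004% to 1.2%, a 300-fold span, so a factor below 2 would rarely change a broad statement that rates are low. It does change the printed limit. The article also wants the method to perform across a range of transmission intensities, so an offset that works only near zero prevalence is not a correction.

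**Conclusion.** The point holds in a limited form. The target is infection prevalence, and the stated model estimates confirmed PCR positivity. For any net sensitivity below 1, the result is lower than a sensitivity-corrected analysis would give.

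With the prior on true prevalence, the correction to the mean and limit is a factor of about 1.03 to 1.52 over assumed sensitivities of 0.95 to 0.60 and one to six rounds. It averages 1.15 to 1.30 on the zero-positive limit under the uniform 0.6 to 0.9 assumption. Whether the limit then misses the truth depends on prevalence. Below roughly 1e-4 it generally still covers. Above that, coverage drops, and it drops further as sensitivity falls and prevalence rises. These sizes describe the unweighted conjugate core, with perfect specificity and constant prevalence.

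**What to change.** 1. Label the output of the model as it stands *prevalence of confirmed PCR positivity*.
2. Report infection prevalence beside it, with the count modelled as Poisson(n × sensitivity × prevalence). Either put a stated prior on net sensitivity or tabulate results over a stated range, using the laboratory's own validation data where available. Net sensitivity should cover the swab, the first PCR and the confirmatory test together. State how discordant samples are counted, and whether the Gamma prior applies to true prevalence or to the detected rate.
3. Vary test sensitivity in the simulations already planned, alongside transmission intensity.

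No new data are needed. The cost is a few lines of analysis code and one stated assumption, a somewhat wider limit, and an infection estimate that depends on the sensitivity range chosen. Printing both figures keeps that dependence visible.
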